## 7.2 Exclusion criteria

Patients are ineligible to participate in the study, if they have any of the following:

- Pregnancy (dipstick pregnancy test)
- Lactating mothers
- Last intake of ivermectin (IVM) less than 4 months ago
- Intake of anti-filarial antibiotic treatment (tetracycline) less than 12 months ago
- Evidence of tuberculosis (clinical aspects)
- Evidence of clinical aspects of HIV infection
- Evidence/previous diagnosis of chronic diseases (urolithiasis, liver cirrhosis, congestive heart failure, chronic lung diseases, chronic infections other than filariae, viral hepatitis)
- Evidence of autoimmune diseases and allergies
- Evidence of acute infection (haematuria, cough, fever). Evidence of clinically significant neurological, cardiac, pulmonary, metabolic, rheumatologic or renal disease as far as can be assessed by history of individuals, physical examination, and/or laboratory examinations
- Childbearing potential and not willing or able to use methods to prevent a pregnancy for the entire treatment duration in addition to hormonal contraception (e.g. condoms) unless surgically sterilized/hysterectomized or any other criteria considered sufficiently reliable by the investigator
- Behavioural, cognitive or psychiatric disease that in the opinion of the trial clinician affects the ability of the participant to understand and cooperate with the study protocol
- Laboratory values which will lead to exclusion
  1. Haemoglobin < 8 g/dL
  2. Neutrophil count < 500/ $\mu\text{l}$ \*
  3. Platelet count < 100 000/ $\mu\text{l}$
  4. Creatinine > 2 times upper limit of normal
  5. AST (GOT) > 2 times upper limit of normal
  6. ALT (GPT) > 2 times upper limit of normal
  7.  $\gamma$ -GT > 2 times upper limit of normal
  8. HbA1c above 44mmol/mol Hb (6%)

\*The neutrophil exclusion criteria was adjusted due to the obtained data from 2000 screened participants. All participants displayed a decreased mean neutrophil blood level independent of infection status and general health indicating a regional trend towards reduced neutrophil numbers. This circumstance for the African population was described previously [34-37].

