### 6.4 Outcomes and variables

Determination of fasting blood glucose levels, glycated hemoglobin (HbA1c), total cholesterol, triglycerides, and high density lipoprotein cholesterol (HDL-C), low-density lipoprotein cholesterol (LDL-C) and liver function enzymes-AST (aspartate aminotransferase), ALT (alanine aminotransferase), alkaline phosphatase (ALP), and  $\gamma$ -glutamyltranspeptidase (GGT), adipokines (adiponectin, leptin, visfatin, resistin, and

plasminogen activator inhibitor-1 (PAI-1)), pancreatic hormones (Glucagon, Insulin and C-peptide) and gut hormones (ghrelin, glucose-dependent insulintropic polypeptide (GIP) and glucagon-like peptide 1 (GLP-1)). To assess kidney function, serum creatinine, urea and urine albumin will be measured. Albumin concentrations will be measured in fasting urine samples. Microalbuminuria and macroalbuminuria will be diagnosed if the albumin excretion is between 30 and 299 µg/mg and was  $\geq 300$  mg/g of creatinine, respectively. We will assess the impact of filarial infection on gut leakage during obesity by screening the plasma for the microbial translocation markers LPS-binding protein (LBP), endogenous endotoxin-core antibodies (EndoCAb), systemic LPS levels and intestinal fatty acid-binding protein (iFABP). Acute-phase proteins alpha-2-macroglobulin ( $\alpha$ -2M), C-reactive protein (CRP), haptoglobin, and serum amyloid A protein (SAA).

- Insulin resistance calculated based on HOMA-IR
- Total and differential leucocyte counts as well as absolute and relative quantification of naïve, effector and central memory CD4+ and CD8+ T cells, regulatory T cells, NK cells, subset of monocytes, dendritic cells and B cells in whole blood via flow cytometry in a subset of n=30 in each group
- Frequencies of intracellular cytokine-producing cells of in vitro whole blood cell cultures in response to PMA/ionomycin, anti-CD3/anti-CD28, Pam3Cys, LPS, or palmitic acid determined by flow cytometry in a subset of n=30 in each group
- Pro- and anti-inflammatory cytokines and chemokines in plasma, whole blood culture supernatants analysed by multiplex cytokine assays
- Total humoral immune responses in serum IgG1, IgG2, IgG3, IgG4, IgA, and IgE and antibody titres against parasite antigens quantified by ELISA
- Microfilariae burden in *Mansonella*, *Loa loa* and *O. volvulus* patients.

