## 10 STATISTICAL CONSIDERATIONS

### 10.1 Sample size justification and statistical analysis

This is a partially randomized controlled open label pilot trial to gain first experience on the impact of infections with the filarial nematodes *O. volvulus* and *M. perstans* on the metabolic profile and the systemic immune response in lean and obese patients. As there is limited data that exists to inform on study design, we will use 400 persons per group (*O. volvulus* infected, *M. perstans* infected, and endemic non-helminth-infected persons) with half of the participants of each group having a BMI of  $\geq 30$  and the other half of below 25. Thus, cases (those with active worm infections) and controls (worm infection free) will be included at a case: control ratio of 1:1:1. All *M. perstans* infected patients and all *O. volvulus* infected persons will further be treated in an interventional pilot study to test the changes in the metabolic profile and the systemic immune responses following treatment with doxycycline.

Our primary endpoint will be quantitative changes in insulin resistance (HOMA-IR). The logarithmic transformed HOMA-IR values will be compared between the three obese subgroups with a two-step test procedure. In the first step a one factorial analysis of variance will be used to test the hypotheses of equal mean log(HOMA-IR) values in the three groups at a level of 5%. In case that this hypothesis can be rejected the mean log(HOMA-IR) values will be checked for equality for each pair of groups with a two-sided t-test at a level of 5% for each test. This test procedure maintains a multiple level of 5%. From literature data (33) we expect the logarithm of the HOMA-IR to be normally distributed with a standard deviation of 0.83. With the planned sample size of 200 cases per group the intended test procedure then has a power of 80% to detect a deviation of 0.3 in the mean log(HOMA-IR) values between two of these groups. This is equivalent to reduction of 25% of the HOMA-IR in comparison between these two groups.

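### The HbA1c exclusion limit in section 7.2 pairs 44 mmol/mol with 6%, which are not the same value, and the protocol names no governing unit

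*Protocol*

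**What the plan says.** Protocol section 7.2 opens its numbered list with "Laboratory values which will lead to exclusion", and item 8 of that list reads "HbA1c above 44mmol/mol Hb (6", completed by a per cent sign and closing bracket. The limit appears once. Neither the synopsis nor the inclusion criteria in 7.1 repeats it, and nothing in the protocol gives a conversion rule, a rounding rule or the unit in which the assay reports.

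HbA1c is also a study variable. Section 6.4 begins its list of outcomes with "Determination of fasting blood glucose levels, glycated hemoglobin (HbA1c), total cholesterol, triglycerides, and high density lipoprotein cholesterol (HDL-C", and section 8.2 has HbA1c measured at screening before treatment and at both follow-ups. Section 10.1 states "Our primary endpoint will be quantitative changes in insulin resistance (HOMA-IR" and makes its main comparison on log HOMA-IR among the obese subgroups.

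On how screening is run, section 8.1 describes one process, carried out in the villages by one research team, for all volunteers. The synopsis expects about 5000 people to be screened, and the footnote to 7.2 refers to data from 2000 already screened.

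**The concern.** An eligibility limit has to sort every result to one side or the other. Here the text gives a value in one unit and, in brackets, a value in another unit that does not correspond to it. Staff with a result in mmol/mol and staff with a result in per cent could both follow the protocol to the letter and reach opposite decisions about the same person.

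What is at stake is consistent application of a hard exclusion on a glycaemic variable, in a study whose primary endpoint is insulin resistance. The people concerned sit at the upper end of the glycaemia that the trial can enrol. Sample size and significance level are not affected.

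**Working it through.** **Inputs.** From section 7.2: exclusion above 44 mmol/mol, and 6% as the bracketed equivalent. From section 10.1: SD of log HOMA-IR 0.83 and detectable difference 0.3. Assumed, because the protocol gives no conversion: NGSP % = 0.0915 × (mmol/mol) + 2.15.

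**Step 1: try to reproduce the stated pair.**
- From 44 mmol/mol: 0.0915 × 44 + 2.15 = 4.026 + 2.15 = 6.18%.
- From 6.0%: (6.0 − 2.15) / 0.0915 = 42.1 mmol/mol.

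The pair is not reproduced at one decimal. Consistent pairs would be 44 mmol/mol with 6.2%, or 42 mmol/mol with 6.0%.

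**Step 2: does the rounding of the conversion matter?** Two other common forms were tried.
- 0.09148 × (mmol/mol) + 2.152 gives 6.18% for 44 mmol/mol, and 42.1 mmol/mol for 6.0%.
- 10.929 × (% − 2.15) gives the same two results.

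**Step 3: decision at each whole-number result.**

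| mmol/mol | % | Rule: above 44 mmol/mol | Rule: above 6.0% |
|---|---|---|---|
| 42 | 5.99 | eligible | eligible |
| 43 | 6.08 | eligible | excluded |
| 44 | 6.18 | eligible | excluded |
| 45 | 6.27 | excluded | excluded |

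The two rules disagree above 42.1 and up to 44 mmol/mol, that is, above 6.0% and up to about 6.18%. Reporting the per cent to one decimal does not remove the conflict: 43 and 44 mmol/mol become 6.1% and 6.2%, both above 6.0%.

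**Step 4: can 6% be read as a whole-number rounding?** It is true that 6.18% rounds to 6%. But a value that rounds to 6% lies between 5.5% and 6.5%, which is (5.5 − 2.15) / 0.0915 = 36.6 to (6.5 − 2.15) / 0.0915 = 47.5 mmol/mol. That interval is about 11 mmol/mol wide and reaches well to either side of 44, so a whole per cent cannot operate the limit.

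**Step 5: what would it take to disturb the primary comparison?** Suppose, as an extreme case only, that one group was screened wholly by one figure and another wholly by the other. If a share p of those enrolled under the wider limit lies in the band, and band members average δ higher in log HOMA-IR than the rest, the mean shifts by p × δ. With δ assumed to be one SD (0.83), a shift equal to the detectable difference needs p = 0.3 / 0.83 = 36%. With δ assumed to be two SDs (1.66), it needs p = 0.3 / 1.66 = 18%. Neither p nor δ is given in the protocol.

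**The case against.** The best defence is that the criterion states one limit, 44 mmol/mol, and adds a whole-number gloss. The protocol prints 6%, not 6.0%, and at that precision the gloss is not false. The contradiction also appears only once a conversion from outside the document is supplied.

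Part of this stands. A rounding slip is a likely origin, and the conversion is an assumption. But it is a unit equation whose common forms all give the same answer. The defence also depends on every reader knowing that the first figure governs and the second is approximate, which the protocol does not say. Someone holding a result in per cent has only the bracketed figure to apply.

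A reader might go further and infer that the obese groups are cut at different glycaemic points, so that their baseline HOMA-IR and HbA1c are not comparable. The document does not support that. It would require the figure applied to vary with infection group, whereas section 7.2 sets one criterion for all and section 8.1 describes one screening process. If either figure is used throughout, all groups are truncated at the same point. Changes of device, staff or reporting unit over a long recruitment are possible, but none is described.

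A reader might also want a share of volunteers affected. Assuming normally distributed HbA1c with mean 5.4 to 5.8% and SD 0.4 to 0.5 puts between 4% and 14% of people in the band. The protocol supplies none of those inputs and the answer varies more than threefold across them, so the range is not evidence of size.

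**Conclusion.** The criterion is wrong as written: one hard exclusion limit is expressed as two values that do not agree, and nothing in the protocol says which governs. The disagreement covers results above 42.1 and up to 44 mmol/mol, about 2 mmol/mol or 0.2 percentage points. This rests on the standard IFCC-to-NGSP conversion, and the choice among its common roundings makes no difference.

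The consequence shown is ambiguous eligibility for people in that narrow band. How many there are cannot be computed from the protocol. Bias between groups would be a further step, and would arise only if the figure applied differed between groups. This is a small defect in a rule that is applied at every screening, worth correcting because it is unambiguous to identify and cheap to repair.

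**What to change.** The sponsor should reconcile the two figures in item 8 of the laboratory exclusions in section 7.2. One unit should be named as governing, the other printed as its calculated equivalent to one decimal, and the governing unit used at every screening. Which limit is intended is for the sponsor to state.

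Because screening has already taken place, the sponsor should also establish from the records which figure was applied, and flag anyone with a result above 42.1 and up to 44 mmol/mol. If the records show that one figure was used throughout, stating that closes the matter. If they show mixed use, the flagged records allow it to be tabulated by group.

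The cost is one corrected line, submitted with the next protocol revision under section 9.9, and a check of screening data already held. No new measurements are needed.

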## 8 STUDY PROCEDURES

Ethical approval has already been obtained from the Institutional Review Board of the Faculty of Health Science of the University of Buea, the Cameroon National Ethical Committee

(No2019/03/1153CE/CNERSH/SP) and the Ethical Commission at the University of Bonn (Germany) (Lfd.Nr.046/18). An agreement with local authorities in Littoral region and the community chiefs and elders of the participating villages will also be obtained.

### **8.1 Informed Consent / Patient enrolment**

The study will be explained in detail to the subjects in the local language (Pidgin or French). Each participant will be informed of the voluntary nature of the study and be encouraged to ask questions throughout the duration. Every volunteer will demonstrate the willingness to participate by signature, written or thumbprint on the consent form (see Annex ICF). Following recruitment, patients meeting the entry criteria will be enrolled in the study. Study subjects will be allowed to withdraw from the study at any point of the study. Recruitment will be directly carried out in the villages. Before start of recruitment the research team will visit the village elders to explain the planned study in detail and a pre-screening for age and sex, health, medication status, BMI and infection will occur. At the next visit all villagers will be invited to come to a public meeting where the study will again be explained in detail. After this meeting all interested volunteers, who are between 18 and 60 years old and signed the Informed Consent Form, will be invited for the first screening. In case of subjects below 21 years ICF will be signed by the parents. The screening will be carried out by trained members of the research team under the supervision of Investigators. A medical doctor will be present to do the physical examination and to take the medical history of the volunteers. The blood sampling and ECG will be done by trained and qualified research personnel. The screening will be carried out directly in the villages. The research team will use rooms provided by the village or will bring tents that guarantee the privacy of the volunteers during examination. All volunteers who proved to be eligible for the study during the screening visit will be invited to come to the enrolment which will also be carried out directly in the village.

All patient data will be kept confidential and it will be explained that the samples will only be used for the study defined in the consent form (see Annex ICF). Some of the samples will be transported to the German partner institute at Bonn, Germany for further analysis. The samples will not be used for any commercial purposes but only to ensure and promote technology transfer and long-term sharing of the research results derived from those samples. In case the participant decides to withdraw from the study at any point during the study period, the data collected till far from the participant will be kept and included in the analysis.

### **8.2 Clinical examination and laboratory analyses**

Clinical examinations (Annex CRF) include:

- Medical history including a questionnaire to assess demographic data, socioeconomic factors, educational factors, and behaviour during enrolment
- Skin biopsies (2 skin biopsies of 2 mm diameter at the posterior iliac crest) to assess microfilaridermia during screening, follow-up 1 and follow-up 2
- Urine for dipstick tests (pregnancy test and urine dipstick for haematuria, proteinuria, glucosuria) and metabolic analysis during screening, follow-up 1 and follow-up 2
- Stool for helminths egg counts, including schistosome infections, *Strongyloides* larvae and protozoa during screening, enrolment, follow-up 1 and follow-up 2
- Blood prick test from volunteer's finger for diagnosis of *Mansonella*, *Loa loa* and other filarial infections and blood glucose measurements during screening, follow-up 1 and follow-up 2
- Venous blood will be used to assess white blood cell counts, differential cell blood count, malaria parasites and fasting blood glucose levels, metabolic and immunological parameters during enrolment, follow-up 1 and follow-up 2

- HbA1c, cholesterol, triglycerides, HDL-C, LDL-C, AST, ALT, ALP, CGT, adipokines, Glucagon, Insulin, C-peptide, Ghrelin, GIP, GLP-1, HOMA-IR, serum creatinine, urea and urine albumin, LBP, EndoCAB, LPS, iFABP,  $\alpha$ -2M, CRP, haptoglobin, SAA during screening (before treatment), follow-up 1 and follow-up 2
- Height, weight, waist circumference, body fat (using a weight scale body fat analyser), blood pressure, electrocardiogram measurements during screening, follow-up 1 and follow-up 2

## 9 SAMPLE COLLECTION AND DATA MONITORING

### 9.1 Study monitoring

Principal Investigators will monitor all aspects of the study, with respect to current GCP, to ensure compliance with government regulations. The objectives of a monitoring visit will be to ensure

- i) Availability of the signed ICF (Annex ICF)
- ii) GCP adherence to the protocol
- iii) Accuracy and completeness of the CRFs (Annex CRF) with source data. During the monitoring visit, the investigator (and/or designee) and other study personnel should be available to discuss the study and any relating issues. Furthermore, all official study documentation must be available for review at all times.

### 9.2 Sample collection: skin biopsies and blood taking

Two skin biopsies will be taken during enrolment, follow-up 1 and follow-up 2 from the right and the left posterior iliac crest to determine the microfilaria load per milligram of skin. After disinfection of the skin areas, the skin will be snipped using a surgical device (2mm Holth Corneoscleral or Walzer punch). The wound will be covered with a plaster to avoid infection. Biopsies will be incubated in saline overnight and the microfilariae counted using a microscope. The skin biopsies will be weighed to determine the microfilariae per mg of tissue.

At baseline and both follow-up time points, after overnight fasting, volunteers will be also asked to provide urine (collected in clean pots labeled with the barcodes of each study participant) and venous blood samples (2x9ml in EDTA) will be drawn by venous puncture according to standard procedures for immune profiling (immunoglobulin subclasses, cytokines/chemokines via ELISA, PCR, multiplex ELISA, and immune cell profiling, leucocyte activation and cytokine production by flow cytometry) and metabolic/biochemical profiling (HbA1c, cholesterol, triglycerides, HDL-C, LDL-C, AST, ALT, adipokines, Glucagon, Insulin, C-peptide, Ghrelin, GIP, GLP-1, HOMA-IR). White blood cell counts, malaria parasites, as well as fasting blood glucose levels will be also determined in venous blood samples. One finger of the volunteer's hand will be pricked with a sterile lancet and 10 $\mu$ l of blood will be directly used to determine blood glucose levels and 20  $\mu$ l of the same blood draw will be used to check for the presence of microfilariae. 50  $\mu$ l of blood will be additionally transferred from the pricked finger into tubes containing 950  $\mu$ l of 3% acetic acid and mixed thoroughly to lyse the red cells to confirm the results. The finger wound will be covered with a plaster to avoid infection. The risk, taking part in this study, is associated with the risk of developing a bruise at the point of needle insertion with possible colouration of the skin.

### 9.3 Intervention pilot study

An intervention study analyzing the kinetic of changes in the metabolic and immunological profiles after anti-filarial treatment will be conducted. All patients of the *M. perstans* infected obese and lean subjects will receive anti-filarial therapy (Fig. 1). The known treatment option for *M. perstans* infections with 200mg of doxycycline daily for 6 weeks will be used (28, 29) since ivermectin is known not to deplete the *Mansonella* adult worms and to have only modest effect on microfilariae (30). This doxycycline therapy will permanently sterilize the female adult *Mansonella* worms and lead to the death of the adult worms over time. All onchocerciasis patients will also receive the anti-filarial therapy with 200mg of doxycycline daily for 6 weeks, which was previously shown to sterilize the female adult *Onchocerca* worms and lead to the death of the adult worms over time (31, 32). Patients co-infected with *Onchocerca* and *Mansonella* will also be treated with 200mg of doxycycline daily for 6 weeks. As *L. loa* does not contain *Wolbachia* endosymbionts, doxycycline treatment will not affect *L. loa* co-infection. Onchocerciasis patients, *M. perstans* infected patients, *L. loa* infected individuals and endemic controls will receive single dose of 400 mg albendazole every three months with a total of 4 treatments for the elimination of soil transmitted helminths. Treatment of *L. loa* infected individuals with albendazole does not kill the adult worms, but reduces the microfilariae load in a safe and well tolerated manner. Treatment of onchocerciasis patients with ivermectin as originally intended is not an option, as the study site selected for our study received more than 10 years of ivermectin MDA and suboptimal responses were observed with reoccurring microfilaridermia within less than one month. As a 6-week treatment with doxycycline is not ethically acceptable for endemic controls, those participants will only receive albendazole treatments. Although *Mansonella* infections do not cause pathology and there is no MDA program for mansonellosis we are now treating all *Mansonella* patients with doxycycline. The benefit of the *Mansonella* patients to receive doxycycline may be a lower risk to acquire co-infections such as tuberculosis and HIV. On the other hand we hypothesize that clearance of the *Mansonella* infection by doxycycline therapy may have a negative effect on insulin sensitivity in obese patients, but this needs scientific evidence and was not sufficient to convince the participants of the study not to be treated for the duration of this study. An overview of the groups and subject numbers is provided in Fig.1.

Doxycycline (tablets, film-coated) will be administered ad personam by the study clinician directly in the villages under supervision (directly observed treatment, DOT) for 6 weeks. Doxycycline 200mg (2 tablets a 100mg) will be administered orally once daily for 6 weeks. The dosage will be reduced to 1 tablet a 100mg in participants with a body weight  $\geq 40\text{kg}$  and  $< 50\text{kg}$ . Individuals below 40kg will not be treated with doxycycline.

All participants of this study will be also treated by the study clinician directly in the villages under supervision (directly observed treatment, DOT) with 400mg albendazole (one tablet) once every three months for a total of four treatments. This treatment clears intestinal helminths and is used for MDA treatment.

Participants positive for *L. Loa* will receive the above described albendazole treatment and will be followed up on after 12 and 18 months.

All subjects will be followed up at 12 and 18 months after treatment and sample collections as described under 6.2 will be performed. Patients will be screened for helminth infections and the impact of possible re-infections following doxycycline or ivermectin treatment will be taken into account. Compliance to the treatment will be confirmed by collecting empty drug containers during the visit of the study subjects. Subjects will be monitored throughout the study for any adverse effects.

Each treatment will be documented and potential severe adverse events will be documented in the CRF (see Annex CRF).

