### 9.3.2 *Precautions to mitigate drug specific risks (Doxycycline)*

#### Photosensitivity

Photosensitivity manifested by an exaggerated sunburn reaction has been observed in some individuals taking tetracyclines. Patients apt to be exposed to direct sunlight or ultraviolet light will be advised that this reaction can occur with tetracycline drugs. Treatment will be immediately stopped at the first evidence of skin erythema.

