#### *Clostridium difficile* –associated diarrhea

*Clostridium difficile*-associated diarrhea (CDAD) has been reported with the use of nearly all systemic antibacterial agents, including Moxifloxacin, with severity ranging from mild diarrhea to fatal colitis. Therefore participants in this study with diarrhea will be monitored especially for CDAD and in case of suspected or confirmed CDAD treatment will be immediately stopped and the patient will be treated for CDAD as appropriate (fluid and electrolyte management, protein supplementation, antibacterial treatment of *C. difficile*, surgical evaluation if clinically indicated) until recovery. Since CDAD has been reported to occur over two months after the administration of antibacterial agents, patients will be strongly encouraged to report any severe diarrhea to the research team also after completion of the treatment.

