#### Rare (< 0.1%) side effects:

Gastrointestinal: pancreatitis

Genitourinary: proteinuria

Hematologic: low red cell count, pancytopenia, thrombocytopenia

Musculoskeletal: bone pain

Ocular: ocular maculopathy

Frequency not reported:

Hematologic: granulocytopenia, agranulocytosis

Hepatic: hepatotoxicity, hepatic abnormalities\*, jaundice\*, hepatocellular damage\*

\*severe hepatic adverse events reported during prolonged higher dose treatment

Ocular: retinal damage

Postmarketing reports:

Dermatologic: erythema multiforme, Stevens-Johnson syndrome, reversible alopecia (thinning of hair and moderate hair loss)

Gastrointestinal: diarrhea

Hematologic: aplastic anemia, bone marrow suppression (mainly in patients with liver disease), neutropenia, agranulocytosis, pancytopenia

Hepatic: acute liver failure, elevated liver enzymes and hepatitis

Musculoskeletal: rhabdomyolysis

Nervous system: somnolence, convulsion, headache

Ocular: blurred vision

Renal: acute renal failure

Other: asthenia, fever

**9.3.5 Adverse events**Documenting, Recording and Reporting Adverse Events

At each contact with the subject, information regarding adverse events will be elicited by appropriate questioning and examinations and will be:

- immediately documented in the subject's medical record/source document
- The study clinicians/physicians will visit the participants in their villages every day during the treatment period to closely supervise possible (severe) adverse events. Additionally the phone numbers of the trial clinicians will be handed to the village health workers as well as to the participants. In case of an emergency between the visits, the clinicians have to be called and will come to the participants whenever needed. In case the participant has to go to a hospital for further examinations and treatment, the transport and medical care will be paid by the research team. An insurance for participants and the medical personal involved in the project and directly in charge of the patients will be provided.

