## **9.12 Study Monitoring**

To ensure accurate, complete, consistent, and reliable data, and ensure the patients' safety, the investigator's site and trial procedures will be monitored by the ministry of public health, the Division of Operational Research in Health (DROSS). The public health's representative will visit the site:

- to evaluate the progress and recruitment of the trial,
- to review the source documents and CRFs for protocol compliance, accuracy and validation,
- to assess facilities and equipment,
- to check for protocol compliance,
- to assure the (severe) adverse events reporting,
- to verify proper handling and dispensing of the IMP(s), and other factors.

The investigator agrees to cooperate with the monitor to ensure that any problems detected in the course of these monitoring visits are addressed and resolved, and therefore ensures the accuracy and consistency of the trial with GCP and all applicable laws. The investigator allows the monitor to have access to all trial related original data and documents relevant for the monitoring of the trial.

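### The only protocol rule sending adverse events to the CRF names severe ones, so non-severe events, including those that stop doxycycline, have no stated path to the analysed database

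*Protocol*

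**What the plan says.** Protocol, Section 9.3 (Intervention pilot study), sets a broad surveillance aim: "Subjects will be monitored throughout the study for any adverse effects". On recording it says: "Each treatment will be documented and potential severe adverse events will be documented in the CRF".

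Section 9.3.5 (Adverse events) covers every event: "At each contact with the subject, information regarding adverse events will be elicited by appropriate questioning and examinations and will be". The list that follows gives one destination for them: "immediately documented in the subject's medical record/source document". Its next item describes daily clinician visits during treatment, telephone access and paid hospital care. It names no step to the CRF, the database, the sponsor or the safety committee.

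Section 9.3.2 lists events that stop doxycycline. For photosensitivity: "Treatment will be immediately stopped at the first evidence of skin erythema". Suspected or confirmed *Clostridium difficile*-associated diarrhea (CDAD) and superinfection also lead to an immediate stop. For the period after treatment, the CDAD paragraph adds: "patients will be strongly encouraged to report any severe diarrhea to the research team also after completion of the treatment".

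Section 9.12 gives the external monitor, among other tasks, this one: "to assure the (severe) adverse events reporting".

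**The concern.** The protocol elicits all adverse events, but its one sentence about putting them on the CRF names a subset defined by severity. Severity (how intense an event is) and seriousness (what it leads to, such as hospital admission) are different attributes, and the protocol uses only the first. A moderate event that sends a participant to hospital is the usual example of an event that a severity filter misses. Here the filter also misses events that the protocol treats as important enough to end treatment.

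At stake is the safety record of a six-week antibiotic course in about 800 people. Half of them have *Mansonella* infection, which Section 9.3 says causes no pathology, so tolerability weighs in the benefit-risk judgement. If non-severe events stay in individual source records, the database cannot give their rates, and an interrupted course may appear without the event that caused it.

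**Working it through.** The plan gives no figure for this point to reproduce. The check sets the passages side by side and then adds simple arithmetic for scale.

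**1. Where each kind of event is sent**

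| Step | Section | Scope stated |
|---|---|---|
| Surveillance | 9.3 | any adverse effect, throughout the study |
| Elicitation | 9.3.5 | all adverse events, at each contact |
| Source record | 9.3.5 | all elicited events |
| CRF | 9.3 | potential severe events |
| REDCap | 9.7 | what is on the paper CRF, double entered |
| Analysis | 9.7 | the locked database |
| Monitor's event task | 9.12 | 'severe' in brackets, so scope unclear |

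The scope narrows at the CRF step, and everything after it inherits that limit. Section 9.7 also makes the investigator responsible for the clinical, safety and laboratory data entered on the CRFs, with no severity limit. That sentence concerns responsibility for what is entered; it does not say which events must be entered. If it is read as covering all safety data, it conflicts with Section 9.3.

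**2. Stops against the CRF rule**

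The erythema stop applies at first evidence. The superinfection stop applies if one occurs. The CDAD stop applies on suspicion, and that paragraph describes a range from mild diarrhea to fatal colitis. None requires the event to be severe. Section 9.3 has each treatment documented, so missed doses should be visible, but no sentence requires the reason to be recorded on the CRF.

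**3. Terminology**

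The protocol text does not use the word 'serious'. It gives no seriousness definition, severity scale or reporting timeline for adverse events. Sections 9.3.5 and 9.12 put 'severe' in brackets, which can be read as severe events only or as all events including severe ones.

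**4. What the safety committee can see**

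Section 9.12 has the ministry's operational research division review source documents as well as CRFs. Section 13.8 makes the same division the safety committee. Non-severe events are therefore within its sight, though as individual records; no cumulative table of them is provided for.

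**5. Scale**

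Section 6.3 plans 200 obese + 200 lean = 400 people with onchocerciasis and 200 + 200 = 400 with *M. perstans*, all for doxycycline: 400 + 400 = 800. Expected number = 800 × rate listed in Section 9.3.1:

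- rash: 800 × 0.04 = 32
- diarrhea: up to 800 × 0.06 = 48
- vomiting: 800 × 0.081 = 64.8, about 65
- nausea: up to 800 × 0.134 = 107.2, about 107
- headache: up to 800 × 0.26 = 208

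These are counts of people with an event of any severity. They are not counts of stops: listed rash is not the erythema trigger (photosensitivity appears under frequency not reported), and listed diarrhea is not CDAD.

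**The case against.** The strongest reply is that Section 9.3 does not say that only severe events go on the CRF. It cites a CRF annex that is not in the public text and may hold a full adverse-event page with a reason for stopping. Section 9.1 has monitoring check the completeness of CRFs against source data, and Section 9.7 leaves data-handling detail to a data management plan. This stands to a point: loss of these events is not shown. But no sentence requires their entry, and if the annex has such a page, the protocol text misdescribes it. Nor can a statistical analysis plan analyse events that were not collected.

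Several stronger readings are tempting, and the document does not support them:

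- *Non-severe events never reach the database or the safety committee.* The first part is an inference made without the CRF annex. The second fails because the committee is the body that reviews the source documents.
- *After treatment, only severe diarrhea is asked about.* Section 9.3.5 requires questioning at each contact, and the supervised three-monthly albendazole doses are contacts. What remains is a mismatch of wording inside the CDAD paragraph and with Section 9.3.5.
- *Almost none of the listed events would be severe.* The protocol gives no severity split.
- *The HOMA-IR comparison is distorted by unexplained stops.* Section 10.1 compares three obese groups and specifies no comparison of fully with partly treated participants.

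**Conclusion.** The point holds as an inconsistency in what is recorded where. Sections 9.3, 9.3.5, 9.7 and 9.12 disagree on the scope of adverse-event recording. Followed as written, non-severe events, including any behind a doxycycline stop or a hospital visit, have no stated path to the data that will be analysed, while remaining available to the monitor and safety committee in source documents.

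The number of records affected cannot be computed. It depends on the CRF annex and on the share of events judged severe, and neither is given. The 800 planned for doxycycline and the expected counts show only that the events at issue are common. The conclusion assumes that Section 9.3.5 as published is complete and that staff follow the protocol text where it and the annex differ. The change is a worthwhile, inexpensive improvement; the study's primary analysis does not depend on it.

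**What to change.** Reconcile Sections 9.3, 9.3.5, 9.7 and 9.12 around one rule: every elicited adverse event is entered on the CRF and in REDCap. For each event record start and end dates, severity, seriousness as a separate field with a definition, relation to doxycycline or albendazole, and action taken on treatment, including the reason for any stop. Where reporting is meant, replace the bracketed 'severe' with 'serious'.

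In the CDAD paragraph of Section 9.3.2, reconcile the request to report severe diarrhea with that paragraph's own range starting at mild diarrhea and with the questioning required by Section 9.3.5. Which clinical rule applies is for the sponsor to decide.

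The cost is amendment wording, with the renewed ethics permission that Section 9.9 requires for protocol revisions, some CRF space and extra data entry. No new visit or procedure is needed, because the events are already elicited and written down. For anyone already treated, entries can be made from the source record. If the CRF annex already has these fields, only the protocol wording needs to change.
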